### Resting-State and Voxel-Based Morphometry

#### Cortical Thickness

MPRAGE images will be processed using the pipeline established in Free Surfer [52]. Cortical thickness from various regions of interest (ROIs) is then determined as the mean of difference between WM and pial surfaces. We will generate an average surface map to which each surface map will be aligned followed by generation of a group difference map.

#### Connectivity Analysis

Following the preprocessing steps as described earlier, we will register all the 300 volumes collected for rs-fMRI to the first volume of the time series. As differential head motion between groups can introduce artifacts, we will equate the PD and control groups with a *scrubbing* procedure to remove volumes compromised by motion [53]. The resting-state series will then be registered to the high-resolution structural images, spatially normalized to standard space using the MNI atlas, and resampled to a spatial resolution of 2.0 mm isotropic and then spatially blurred using a 5-mm Gaussian kernel. The segmented masks (GM, WM, and CSF) created as part of the measurement for cortical atrophy will account for time series variance from the nonneuronal contributions of CSF and WM. In addition, the 6 standard movement parameters from registration will be regressed out of the 4-dimensional data. Graph-theoretic analysis on selected ROIs that are relevant to PD cognition based on our hypotheses will be performed and expanded to a more global approach using Graph Analysis Toolbox (GAT) [54]. The ROI method will consider regions such as *caudate, putamen, cingulate, orbitofrontal, dorsolateral prefrontal cortex (DLPFC), superior and inferior parietal, posterior and anterior visual cortex, superior and medial temporal.* Pairwise correlations between mean BOLD time series using ROIs will be utilized to create functional connectivity matrix followed by the Fisher transformation to z score association matrix. Various topological features of the networks will be captured at the global and regional level such as total connectivity, normalized clustering coefficient, normalized path length, density, global efficiency, and betweenness centrality [55]. Between-group comparisons will be made using a 2-sample *t* test after correcting for multiple comparisons with significance set at *P*<.05. To determine the relationship of the network topology with cognition, we will correlate all subtests of the neuropsychological and visuoperceptual assessments using the Pearson correlation coefficient comparing PD with normal cognition across 4 years and PD with cognitive progression.

Using a more global approach, we will perform cortical/subcortical parcellation to define 200 brain regions to identify and understand the influence of other networks on PD network topology and to assess whether taking such interactions into account influences predictions in PD outcomes. The extracted time courses from each of these regions will be correlated against one another to produce a 200×200 adjacency (correlation) matrix, followed by the Fischer transformation to z score association matrix. Similar metrics will be extracted as in the case of the limited ROIs described above.

Activation maps from fMRI will be analyzed using statistical parametric methods, and contrasts will be conducted using multiple regression with the General Linear Model, allowing for multiple predictors to be built into the model [56]. Regressors representing the experimental conditions of interest will be modeled with a hemodynamic response function and entered into the multiple regression analysis using both fixed- and random-effects models. Whole-brain statistical analyses will be conducted, and statistical parametric maps will be generated to examine brain regions that differ in activation between the groups and conditions (encoding and immediate and delayed recall). These analyses will be performed in each group separately using a repeated-measures analysis of variance model and then between groups (PD and PD-MCI). We will inspect the entire brain for areas of activation, and areas will be considered significant if they exceed a threshold of q<.001 (False Discovery Rate). We will evaluate the relationship between brain activation and cognition inside and outside the scanner.

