### Inclusion and Exclusion Criteria

General and specific inclusion and exclusion criteria for both PD patients and controls are reviewed below.

General criteria: (1) age 50 to 77 years to avoid early-onset PD and (2) no evidence of depression on the Beck Depression Inventory (BDI-II >18 is predictive in mild PD) [24].

PD criteria: (1) Diagnosis of idiopathic PD based on the presence of 2 cardinal features [25], (2) improvement with DRT, (3) minimal or mild disease severity based on the Hoehn and Yahr rating scale of <2.5 and motor UPDRS <30 *on* DRT medications [22], and (4) normal or MCI cognition based on MoCA screening (>21) at baseline [26].

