### Statistical Analysis and Power

A sample of 120 PD patients is planned for this study. On the basis of the experience of longitudinal studies in PD, the attrition (mortality and loss to follow-up) is anticipated at 16% for 4 years. Thus, initial recruitment of 120 patients will yield about 100 subjects after 4 years. On the basis of published data, we estimate 70% PD-NC and 30% PD-MCI patients in our sample, and conversion rates of 60% from NC to MCI and 80% from MCI to PDD after 4 years. One of our primary goals is to evaluate progression patterns to determine time-specific differences between groups (NC vs MCI at baseline and PDD vs MCI, MCI vs NC, and PDD vs NC at year 4). Our study will have 80% power to detect medium-to-large average differences across time between the different groups under various within-subject correlations. In terms of predictive models for 4-year outcomes, our study will have 90% power to detect at least 0.86 area under the receiver operating characteristics curve (AUROC) for PDD conversion and 95% power to detect at least 0.74 AUROC for MCI at year 4.

To study differential cognitive progression patterns, generalized estimating equations will be used for describing the longitudinal trajectories of neuropsychological and visuoperceptual performances between PD-NC and MCI groups comparing baseline performance with different time points. The model will provide estimates of PD-MCI versus PD-NC differences at specific time points and longitudinally. Covariates such as age, UPDRS, and visual illusions or hallucinations will be added to the model to enable determination of adjusted differences.

We will investigate the prognostic value of baseline cognition in predicting relative risk for progression to PDD through a multiple logistic regression model. The best combination of baseline measures and covariates included in the prediction model will be selected by the elastic net procedure. Summary statistics of the AUROC will be used to evaluate the predictive power. Sensitivity, specificity, positive predictive value, and negative predictive value will be calculated from the optimal threshold determined by the Youden index. The prediction models will be cross-validated by training and testing methodology.

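### Network metrics are compared by a 2-sample t test and related to cognition by Pearson correlation, without the age adjustment the plan uses for cognitive performance

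*Protocol article*

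**What the plan says.** The Connectivity Analysis section of the protocol article lists six network features: total connectivity, normalised clustering coefficient, normalised path length, density, global efficiency and betweenness centrality. It then fixes the test: "Between-group comparisons will be made using a 2-sample *t* test after correcting for multiple comparisons with significance set at *P*<.05". For the relation to cognition, "we will correlate all subtests of the neuropsychological and visuoperceptual assessments using the Pearson correlation coefficient", and the contrast is between stable normal cognition and progression: "using the Pearson correlation coefficient comparing PD with normal cognition across 4 years and PD with cognitive progression". Adjustment in that section is at the level of the image time series: signal from CSF and white matter is accounted for, compromised volumes are scrubbed, and "the 6 standard movement parameters from registration will be regressed out of the 4-dimensional data".

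Statistical Analysis and Power treats cognitive performance differently. There, "generalized estimating equations will be used for describing the longitudinal trajectories of neuropsychological and visuoperceptual performances between PD-NC and MCI groups", and "Covariates such as age, UPDRS, and visual illusions or hallucinations will be added to the model to enable determination of adjusted differences". For the prediction of dementia, "The best combination of baseline measures and covariates included in the prediction model will be selected by the elastic net procedure"; that model is introduced for the prognostic value of baseline cognition.

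The general entry criterion is "age 50 to 77 years to avoid early-onset PD". Motor UPDRS is measured every year.

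**The concern.** Groups formed by cognitive course are observational. If patients who progress are older than those who stay normal, and a network metric changes with age, an unadjusted t test will show a difference that has nothing to do with cognition. The Pearson correlation has the same weakness when both the metric and the test score fall with age.

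The protections in the section do not address this. Motion regression and scrubbing deal with artefact in the signal. Multiplicity correction deals with chance, whereas this is bias.

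The article predicts lower functional connectivity in occipito-parieto-temporal regions in patients who progress, and would read such a finding as a marker of progression. An age difference could produce the same pattern. Because the test itself is named, this is a stated choice and not a detail left to a fuller document.

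**Working it through.** **Group sizes.** The plan expects 16% attrition from 120 patients: 120 × 0.84 = 100.8, which reproduces its figure of about 100. Its baseline mix (70% normal cognition, 30% MCI) and conversion rates (60% normal to MCI, 80% MCI to PDD), applied to 100 completers, give:
- stable normal: 70 × 0.4 = 28
- progressors: 70 × 0.6 + 30 × 0.8 = 42 + 24 = 66
- stable MCI: 6, not used here

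The 28 v 66 contrast is a pooling made for this check. The plan does not list it in this form.

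**Assumptions.** The documents give no age SD, age gap or age-metric correlation. Assumed: SD 7 years, gap 3 to 5 years, within-group correlation r of 0.2 to 0.5, and no true network difference.

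**Formulas.** Spurious standardised difference d = r × gap / 7. Noncentrality = d × √(28 × 66 / 94) = 4.43d. Rejection comes from the two-sided noncentral t distribution with 92 degrees of freedom. The plan corrects for multiplicity but names no method, so the last column assumes Bonferroni over the six listed metrics, 0.05 / 6 = 0.0083.

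| Gap (years) | r | d | Rejection at nominal 5% | Rejection at nominal 0.8% |
|---|---|---|---|---|
| 3 | 0.2 | 0.086 | 6.6% | 1.3% |
| 5 | 0.3 | 0.214 | 15.6% | 4.4% |
| 5 | 0.5 | 0.357 | 34.7% | 13.9% |

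For baseline normal v MCI at 70 v 30, the rates at nominal 5% are 6.8%, 16.3% and 36.7%, so the choice of contrast matters little.

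**Does adjustment work?** Simulations of 10,000 data sets at 28 v 66, with an imbalance of 0.25 to 0.75 SD and r of 0.2 to 0.4, gave 5.7% to 26.7% rejection unadjusted. With the covariate in a linear model the rate was 4.5% to 5.2%.

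**Correlations.** If age correlates 0.3 with the metric and 0.4 with the score (assumed), the spurious correlation is 0.3 × 0.4 = 0.12. At n = 66, Fisher z × √63 = 0.96, so about 16% of tests reject at nominal 5%.

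**Power.** Take a true d of 0.64, which gives 80% unadjusted. Adjustment scales the residual variance by (1 − r²) and inflates the variance of the group effect by 1/(1 − R²), where R² is the overlap of group and age. For gaps of 0 to 5 years, power becomes about 78% to 82% at r = 0.2, 80% to 84% at r = 0.3 and 87% to 90% at r = 0.5.

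**The case against.** **The groups are inferred.** The t-test sentence names none, and the only groups named earlier in that section are PD and control. This stands as a limit. The next sentence and the prediction about progressors make cognitive groups the most plausible reading, but it is a reading.

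**An adjusted step comes later.** The elastic-net model admits covariates and is cross-validated, and the Conclusions speak of a predictive model that uses neuroimaging markers, so a biomarker claim need not rest on the t tests alone. This mitigates in part. That model is introduced for baseline cognition and does not alter the connectivity tests. Nor does the General Linear Model with multiple predictors, which is stated for the task activation maps.

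**The size is assumed.** This is correct. At the low end the inflation is small, and the 35% figure needs the largest gap and the largest correlation together, at an uncorrected 5% that is not the plan's rule. No calculation here covers UPDRS, whose baseline range the entry limits (Hoehn and Yahr below 2.5, motor UPDRS below 30) narrow.

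**Scores may be age-normed.** The Methods overview uses cutoffs of −1.5 and −2 SD, which suggests norms. If normed scores are correlated, the age path largely closes. The article does not say which scores are used.

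**Stronger readings that the article does not support.** A reader might infer that the plan concedes an imbalance in age and motor severity between cognitive groups. It says only that covariates will be added to obtain adjusted differences, which admits no imbalance. A reader might also want UPDRS-III at the analysed visit in the main model. At year 4 that is a post-baseline variable, and motor and cognitive decline may share the pathology under study, so conditioning on it could remove real signal. Nor can the cortical-thickness map be called unadjusted: that section names no test, and a condensed article may leave the detail elsewhere.

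**Conclusion.** The point holds for age. The article fixes tests for the network metrics that cannot carry a covariate, while it adjusts the cognitive-performance model for age and UPDRS. If the groups are defined by cognitive course, an age difference can be reported as a network marker of progression.

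How often cannot be known from the document. Over the assumed range, the error per metric is about 1.3 to 7 times nominal at an uncorrected 5% (6.6% to 34.7%), and about 1.6 to 17 times nominal under Bonferroni over six metrics (1.3% to 13.9% against 0.83%). The lower ends are minor; the upper ends require a 5-year gap and a correlation of 0.5. The case rests on bias. A power gain of 5 points or more needs a correlation near 0.5.

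For motor severity the concern is plausible, since caudate and putamen are among the regions, but it is not quantified and supports a sensitivity analysis only.

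**What to change.** In Connectivity Analysis:
- Name the groups compared. Replace the 2-sample t test with a linear model of each metric on group, adjusted for age, and keep the stated multiplicity correction.
- Replace the Pearson correlations with partial correlations adjusted for age. If age-normed scores are used, say so; the change then has little effect.
- Add, as a sensitivity analysis, models that also adjust for baseline motor UPDRS-III. Use the baseline value because the concurrent one may lie on the shared disease pathway.
- Report the unadjusted results as secondary.

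The cost is wording and one degree of freedom. No new data are needed: age is an entry criterion and UPDRS-III is already scheduled. If age differs between groups but is only weakly related to the metric, power falls by about 2 points (80% to about 78% at r = 0.2 with a 5-year gap).

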### Patients

Nondemented idiopathic PD patients will be recruited and evaluated in the *on* medication state. The severity of PD will be graded by the Unified Parkinson Disease Rating Scale (UPDRS-III) motor section [22]. Subjects will be asked to provide consent in accordance with Institutional Review Board (IRB) policies and protected by Health Insurance Portability and Accountability Act regulations, and IRB approval has been obtained from the University of Maryland Baltimore (UMB), School of Medicine. We will recruit 120 PD patients who will be evaluated annually for 4 years on neuropsychological and MRI measures in a 5-year study. Patients will be recruited from the University of Maryland School of Medicine as well as through other advertisements to recruit patients from surrounding areas. Our goal is to complete 100 patients, so we will overrecruit because of anticipated attrition. Potential subjects will be screened, and information regarding the Unified Parkinson’s Disease Rating Scale (UPDRS), mood, Activities of Daily Living (ADLs), and Montreal Cognitive Assessment (MoCA) will be acquired to determine the study eligibility [22,23]. The principal investigator is a clinical neuropsychologist who will review the study and the inclusion criteria and will confirm the diagnosis with the study neurologist who will examine all the patients.

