### Anatomical and Regional Brain Activation Patterns Predictive of Cognitive Progression

Significant atrophy has been associated with transition from MCI to AD [65,66]. However, there is limited work on cortical thinning in early PD, and no longitudinal studies have evaluated cortical thickness measures as biomarkers signaling rapid cognitive progression in PD [17,67]. Critically important to prediction is evaluating differences in patterns of cortical atrophy based on the timing of onset of cognitive progression. This could reveal an anatomical basis for the timing of cognitive decline, thus elucidating the pathological burden in PD [17].

There is an increased interest in studying resting-state brain networks to try and understand interactions between disparate brain regions. Rs-fMRI measures the strength of functional interactions between brain regions based on temporal correlations of the spontaneous fluctuations in the resting-state BOLD signal, such that synchronous temporal changes in signal are functionally connected [68]. Rs-fMRI has been used to test the efficiency and strength of large-scale neuronal networks in the absence of a task. Although rs-fMRI has revealed the natural history of amnestic MCI to AD, very little is known about its efficacy as a biomarker in PD [69,70]. Characterizing differences in PD will elucidate temporal changes in functional networks related to relative changes in frontal, medial-temporal, and posterior cortical regions with cognitive progression and provide neural insights into the timing of pathophysiological changes in PD.

Cortical thickness, voxel-based morphometry, and rs-fMRI will characterize the evolution of regional brain degeneration annually for 4 years in PD patients. We predict a higher rate of cortical thinning and decreased functional connectivity in occipito-parieto-temporal regions in PD patients with cognitive progression.

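### The between-group motion safeguard names a control group that is not recruited, and the stated imaging analyses carry no time term although faster cortical thinning in progressors is predicted

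*Protocol article*

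**What the plan says.** **Who is studied.** Patients: "We will recruit 120 PD patients who will be evaluated annually for 4 years on neuropsychological and MRI measures in a 5-year study". Statistical Analysis and Power: "A sample of 120 PD patients is planned for this study". Table 2 has no row for controls. No number or source of controls appears anywhere in the article.

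**Where controls appear.** Inclusion and Exclusion Criteria opens with "General and specific inclusion and exclusion criteria for both PD patients and controls are reviewed below", but only general criteria and PD criteria follow. Connectivity Analysis warns that groups differing in head motion can produce artifacts, and then says "we will equate the PD and control groups with a" scrubbing procedure.

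**Imaging analyses.** For thickness, Cortical Thickness gives surface alignment "followed by generation of a group difference map", with no groups, visit or model named. For network metrics, Connectivity Analysis says "Between-group comparisons will be made using a 2-sample" t test at 0.05 after multiplicity correction, again naming no groups or visit. It adds Pearson correlations with cognition, contrasting PD patients who stay cognitively normal with those who progress. Task activation is compared between PD and PD-MCI.

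**The prediction.** "We predict a higher rate of cortical thinning and decreased functional connectivity in occipito-parieto-temporal regions in PD patients with cognitive progression". Structural and resting-state MRI are scheduled in each of years 1 to 4.

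**The longitudinal model.** Statistical Analysis and Power plans generalized estimating equations (GEE), with covariates such as age and UPDRS, for neuropsychological and visuoperceptual performance only.

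**The concern.** There are two faults.

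First, the protocol treats unequal head motion between groups as a threat, but the only groups it undertakes to equate are PD and controls. The imaging contrasts that do name their groups lie within PD. If progressors move more than stable patients, no stated group-level step would detect or remove the difference.

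Second, the thickness prediction concerns a rate, and four annual scans are collected to support it. None of the named imaging analyses says that time, change or slope is the quantity compared. If the tests are run on levels, a difference already present at baseline would be read as progression, and the repeated scans would add little.

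**Working it through.** **1. Do the plan's own figures involve controls?**
- Retention: 120 × (1 − 0.16) = 100.8, which agrees with the stated figure of about 100.
- Groups among 100 completers, from the stated 70%/30% mix and 60%/80% conversion rates: 70 NC, of whom 42 convert to MCI and 28 stay NC; 30 MCI, of whom 24 convert to PDD and 6 stay MCI.
- AUROC power against 0.5, two-sided 0.05 (both assumed), with the Hanley-McNeil variance [A(1−A) + (n1−1)(Q1−A²) + (n0−1)(Q2−A²)]/(n1·n0), where Q1 = A/(2−A) and Q2 = 2A²/(1+A), and null variance (n1+n0+1)/(12·n1·n0):
  - PDD, A = 0.86, 24 vs 6: power 0.913 (0.889 with the Obuchowski variance); stated 90%.
  - MCI, A = 0.74, 42 vs 28: power 0.958 (0.953 with the Obuchowski variance); stated 95%.

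All figures reproduce from PD patients alone. That does not prove that no controls exist, but no stated figure depends on them. No power or sample size is stated for any imaging comparison.

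**2. Which groups does the imaging compare?**
- Motion matching: PD and control.
- Correlations of network metrics with cognition: stable normal cognition vs progression, within PD.
- Task activation: PD vs PD-MCI.
- Network-metric t test and thickness map: groups not named.

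The only step that equates motion between groups names a pair that no stated imaging contrast uses.

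**3. Where is time?** The thickness map, the t test and the correlations have no time or change term. The one between-group longitudinal model excludes imaging outcomes.

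**4. Could groups differ at baseline?** Under the stated rates there are 42 + 24 = 66 progressors and 28 + 6 = 34 non-progressors. Baseline MCI makes up 24/66 = 36% of progressors and 6/34 = 18% of non-progressors. Against the 28 patients who stay NC, the contrast is 36% vs 0%. A comparison of levels can therefore reflect baseline status as well as progression.

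**5. What is at stake in power?** Assumptions, none from the article: equal baselines, linear divergence to 0.5 SD by the fourth visit, compound symmetry with correlation ρ, two-sided 0.05, no multiplicity correction.
- Common factor: √(1/66 + 1/34) = 0.211.
- Detectable difference at 80% power: (1.96 + 0.84) × 0.211 = 0.59 SD.
- Fourth-visit levels: Φ(0.5/0.211 − 1.96) = Φ(0.41) = 66%.
- Per-patient slopes: the slope difference is 0.5/3 = 0.167 SD per year. Slope SD is √((1−ρ)/5), because visit times 0 to 3 have a centred sum of squares of 5.
  - ρ = 0.5: SD 0.316, power 70%.
  - ρ = 0.8: SD 0.200, power 98%.
  - ρ = 0.9: SD 0.141, power over 99%.
- Baseline levels: no power beyond alpha.
- Break-even: slopes beat fourth-visit levels when (1−ρ)/5 < 1/9, that is ρ > 0.44.

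**The case against.** The strongest reply is that this is a condensed article. Visit handling, covariates and a longitudinal imaging model are often left to a full protocol or analysis plan, and neither is shown. That would answer a plain omission. It does not answer the control-group contradiction, because the article states two incompatible designs. It answers the second point only in part: the article does choose imaging tests, and it confines its repeated-measures model to cognition.

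Several stronger readings are tempting but not supported:
- *That the imaging comparisons are PD versus control.* Controls appear only in the scrubbing step and the eligibility lead-in. The t-test sentence names no groups, and every imaging contrast that names its groups is within PD.
- *That thickness is analysed by t test.* The t test follows the network metrics. Thickness has only a difference map.
- *That motion is ignored.* Imaging Protocol and Connectivity Analysis both regress out six movement parameters, and compromised volumes are scrubbed. What is missing is a check or adjustment across the PD groups compared.
- *That a t test cannot address a rate.* It can, if applied to per-patient slopes or changes. The text does not say that it will be.
- *That the connectivity prediction is also about rate.* It can be read as a lower level, so the mismatch is clear for thinning only.
- *That the loss is a fixed multiple of the sample size.* A change uses two scans and a level uses one, and the article gives no within-patient correlation.

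**Conclusion.** Two points stand. The control references contradict a cohort made up of PD patients only, and they leave the between-group motion safeguard pointing at a comparison that cannot be made. The predicted higher rate of thinning has no stated analysis with a time or change term, although annual scans are collected and a longitudinal model is already planned for cognition.

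The first point rests on the text alone. The size of the second is illustrative: 66% power for fourth-visit levels against 70% to over 99% for slopes, under the assumptions listed. The advantage shrinks if patients truly differ in slope, which compound symmetry excludes, and it reverses at correlations below about 0.44. The case for modelling change does not depend on that gain, since the prediction is itself about change and the groups are expected to differ in baseline MCI share. This should be corrected, but it does not affect the cognitive prediction models.

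**What to change.** 1. Reconcile Patients, Inclusion and Exclusion Criteria, Connectivity Analysis and Statistical Analysis and Power: delete the control references, or state the source and number of control data.
2. Apply one scrubbing rule to all PD scans, and compare or adjust for residual motion across the PD groups being contrasted.
3. For regional thickness and network metrics, name a longitudinal model over all annual scans, with progression group by time as the tested term. A linear mixed model would serve, as would the GEE already planned for cognition. Adjust for age and UPDRS as in the cognitive model, and for motion. Apply the multiplicity correction already stated for the network metrics to the interaction term.

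The cost is a change of wording and modest extra programming. No new data are needed if the control references are deleted, because the scans and covariates are already planned and motion can be derived from the scans.

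### Network topology is related to cognition by Pearson correlations compared between two groups defined by cognitive course, which cuts n, attenuates each r and makes the two correlations hard to compare

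*Protocol article*

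**What the plan says.** The Connectivity Analysis section of the protocol article states both an aim and a method: "To determine the relationship of the network topology with cognition, we will correlate all subtests of the neuropsychological and visuoperceptual assessments". The sentence goes on to specify the method as "using the Pearson correlation coefficient comparing PD with normal cognition across 4 years and PD with cognitive progression". The sentence just before it plans two-sample t tests between groups, corrected for multiplicity, without naming the groups.

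No expected correlation, power or error level is given for the topology–cognition correlations. The group sizes can be derived from Statistical Analysis and Power. Its assumption on losses is that "the attrition (mortality and loss to follow-up) is anticipated at 16% for 4 years", and its resulting sample is given as "initial recruitment of 120 patients will yield about 100 subjects after 4 years". It assumes "conversion rates of 60% from NC to MCI and 80% from MCI to PDD after 4 years". These rates apply to a baseline mix that it describes as follows: "we estimate 70% PD-NC and 30% PD-MCI patients in our sample". That section also adds age and UPDRS as covariates to the longitudinal model. The connectivity sentence mentions no covariates.

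**The concern.** The aim is to learn how topology relates to cognition, yet the patients are first sorted by how their cognition behaved. Group membership is a coarse version of one of the two variables being correlated, not an outside confounder. Three things follow.

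- Each correlation uses only part of the cohort, and completers with stable MCI drop out.
- Cognitive scores vary less within a group than across the cohort, so each within-group r is smaller than the cohort r.
- Pearson r depends on spread. Two groups sharing one relationship but differing in spread will show different correlations, and the plan intends to compare them.

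A real association could be missed, above all in the stable group. A difference between the two correlations could be taken for a difference in biology.

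**Working it through.** **Inputs from the article.** 120 recruited, 16% attrition, 70/30 baseline split, 60% and 80% conversion.

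**Reproducing the plan's figure.** 120 × (1 − 0.16) = 100.8, which matches the stated 100 or so.

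**Group sizes per 100 completers.**
- Normal to MCI: 70 × 0.60 = 42. Stable normal: 70 − 42 = 28.
- MCI to dementia: 30 × 0.80 = 24. Stable MCI: 30 − 24 = 6.
- Progressors: 42 + 24 = 66. In neither group: 6.

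The article's AUROC powers support these counts. By the Hanley–McNeil method (null 0.5, two-sided 0.05), 0.86 with 24 versus 6 gives 91% (stated 90%), and 0.74 with 42 versus 28 gives 96% (stated 95%).

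**Assumptions, not in the article.** Cohort correlation ρ = 0.30, with 0.40 and 0.50 as alternatives; one test at two-sided 0.05; normal scores.

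**Effect of n alone.** Power ≈ Φ(√(n−3) · atanh(ρ) − 1.96), with atanh(0.30) = 0.3095.
- n = 100: Φ(3.05 − 1.96) = 86%
- n = 66: Φ(2.46 − 1.96) = 69%
- n = 28: Φ(1.55 − 1.96) = 34%

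**Effect of range restriction.** Treat group as a cut at 28:66 on a score whose correlation with the subtest is c. The cut lies at z = 0.53, with normal density 0.347.
- Stable (upper 28/94 = 0.298): tail mean 0.347/0.298 = 1.163; variance 1 − 1.163 × (1.163 − 0.53) = 0.264.
- Progressors (lower 66/94 = 0.702): 0.347/0.702 = 0.494; variance 1 − 0.494 × (0.494 + 0.53) = 0.494.

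With v the variance above, the subtest's variance ratio is u² = 1 − c²(1 − v), and the within-group correlation is ρu/√(1 − ρ² + ρ²u²). At c = 1 this gives 0.30 × 0.513/√(0.91 + 0.09 × 0.264) = 0.16 in the stable group and 0.30 × 0.703/√(0.91 + 0.09 × 0.494) = 0.22 in progressors.

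| c | r stable / progressors | power stable (n = 28) | power progressors (n = 66) |
|---|---|---|---|
| 0 | 0.30 / 0.30 | 34% | 69% |
| 0.5 | 0.27 / 0.28 | 29% | 63% |
| 0.8 | 0.22 / 0.25 | 21% | 53% |
| 1.0 | 0.16 / 0.22 | 13% | 41% |

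**Check with a two-visit model.** Baseline and year-4 composites correlate 0.5–0.85; the lowest 30% at baseline are MCI; the lowest 60% of normal and 80% of MCI patients at year 4 progress; the subtest correlates 0.5–1.0 with the year-4 composite. Within-group r is 0.16–0.28 (stable) and 0.21–0.28 (progressors), with power 12–29% and 40–64%.

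**Sensitivity.** For c from 0.5 to 1:
- ρ = 0.40: stable 20–49%, progressors 67–88%, all 100 patients 99%.
- ρ = 0.50: progressors 88–98%, all patients above 99%.
- If baseline scores are correlated instead, progressors keep 82–98% of the cohort SD, so restriction is weaker.

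**Comparing the two correlations.** The standard error of the Fisher-z difference is √(1/25 + 1/63) = 0.236. For 80% power the difference must be about 2.80 × 0.236 = 0.66, for example r = 0 against r = 0.58. Under a sharp split, one common relationship already produces 0.16 against 0.22.

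**The case against.** The best counter-argument is that the within-group correlation is a legitimate quantity. The plan says it is comparing groups, its hypotheses concern what marks out progressors, and a pooled correlation can arise from a difference in group means alone. This stands in part: attenuation here reflects a different target rather than bias in the strict sense, and a single pooled slope with no group term would drop the comparison the plan names. It does not rescue Pearson r as the tool for that comparison, because r changes with spread.

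The sentence also does not rule out a pooled correlation, nor say which visit's scores are used. Separate correlations are the natural reading, not the only one.

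Three stronger readings are tempting and are not supported.

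- *Range restriction costs a quarter to half of the power.* The article fixes no such figure. At ρ = 0.30, n alone takes power from 86% to 34% and 69%. Restriction removes a further 5–22 points (stable) and 5–29 points (progressors). It exceeds the sample-size effect only in progressors, and only when a subtest nearly equals the score that defines the groups.
- *Most of the signal lies between groups.* For a sharp split the between-group share of subtest variance is 1 − (28 × 0.264 + 66 × 0.494)/94 = 57%. At c = 0.5 it is 0.25 × 57% = 14%. With many separate subtests, the lower figure is the more realistic.
- *The between-group part is discarded.* The preceding t tests may cover it if they use the same groups, which the text leaves open.

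**Conclusion.** The concern holds in a limited form. As it reads, the analysis partly conditions on cognition when the question is how topology relates to cognition. It reduces n to about 28 and 66, leaves about 6 completers out, attenuates each r, and sets up a comparison of correlations that mixes spread with relationship.

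At an assumed cohort r of 0.30, power is about 12–29% and 40–64%, against about 86% for all 100. Most of that loss comes from smaller groups rather than restricted range. A null result in the stable group would carry little information there, since its power does not exceed 34% even without restriction. For progressors the loss nearly vanishes at r = 0.50.

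These figures rest on assumed values for the cohort correlation, for the link between subtest and classification, and for the visit used. The group sizes rest on the article's own rates. The point concerns an imaging aim, not the main prediction model, but the remedy is cheap enough to be worth making.

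**What to change.** In Connectivity Analysis, make the main topology–cognition analysis one regression over all PD completers of the continuous cognitive score on the network metric, adjusted for age and UPDRS. If change in score is the outcome, add the baseline score as a covariate. State which visit's scores are used.

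Keep the planned group comparison as a secondary group-by-topology term, reported as slopes rather than r. Because the groups are selected on cognition, slopes with cognition as the response still shrink within groups: under a sharp split at ρ = 0.30 they are 0.30 × 0.264/(0.91 + 0.09 × 0.264) = 0.08 and 0.30 × 0.494/(0.91 + 0.09 × 0.494) = 0.16. With the network metric as the response, the linear slope stays at 0.30 in both groups. That version should therefore accompany the interaction. Report within-group Pearson correlations as descriptive only, labelled as range-restricted.

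The cost is wording; data and software are unchanged. The one small downside is that the pooled slope, not the pair of group correlations, becomes the headline result.
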